#### Provisions for post-trial care {30}

There are no provisions for the participants in the trial.

Patients are covered by the patient insurance of Copenhagen University Hospital Køge and Hvidovre Hospital respectively.

### Outcomes {12}

#### Primary outcome

The primary outcome, the Knee injury and Osteoarthritis Outcome Score (KOOS_4_), is evaluated at 6 months after the intervention. See Fig. 3 for the study timeline.

The KOOS questionnaire was developed in the 1990s as an instrument to assess the opinion of patient’s with knee osteoarthritis about their knee and associated problems. Since the first publication in 1998, the psychometric properties of the KOOS have been assessed in more than twenty individual studies from all over the world. Furthermore, KOOS 1 year post surgery has been evaluated and compared to other instruments in several reviews [20–23].

KOOS4 constructs an average score for 4 out of the 5 KOOS subscale scores. It was first used by Frobell et al. in 2010 [24]. The fifth subscale concerning activities of daily living (ADL) is excluded in the KOOS 4 as the subscale is thought to add unwanted “noise” to the constructed outcome in active patients with few to none difficulties within ADL [23]. As the population of the trial is active patients, KOOS4 was chosen as the primary outcome.

#### Secondary outcomes (recorded at 3, 6, 12 and 24 months)

##### The Knee injury and Osteoarthritis Outcome Score (including all 5 subscales)

The KOOS holds 42 items in 5 separately scored subscales: KOOS Pain, KOOS Symptoms, Function in daily living (KOOS ADL), Function in Sport and Recreation (KOOS Sport/Rec) and knee-related Quality of Life (KOOS QOL) [23, 25].

The 5 patient-relevant subscales of KOOS are scored separately: KOOS Pain (9 items), KOOS Symptoms (7 items), KOOS ADL (17 items), KOOS Sport/Rec (5 items) and KOOS QOL (4 items). A Likert scale is used and all items have 5 possible answer options scored from 0 (No Problems) to 4 (Extreme Problems) and each of the 5 scores is calculated as the sum of the items included. Scores are transformed to a 0–100 scale, with 0 representing extreme knee problems and 100 representing no knee problems as is common in orthopaedic assessment scales and generic measures. Scores between 0 and 100 represent the percentage of total possible score achieved [23].

The Knee injury and Osteoarthritis Outcome Score is recorded at each follow-up.

##### Tegner Activity scale

The Tegner activity scale was described in 1985 [26] and was designed for ACL and meniscal injuries. The Tegner activity scale has been frequently used as a patient-administered activity rating for patients with different knee disorders. The Tegner score is a patient-administered score of activity level with 11 defined grades, from 0 representing disability because of knee injury to 10 (professional level soccer) [26].

Tegner activity score is recorded at each follow-up.

##### Work status

Changes in work status. Is the patient working full- or part time or not working. Our study groups are primarily patients who are eligible to work, and not patients already retired.

The patients are asked if they work full time, part time or not working. The patient answers if the work is hard physical work, moderate physical or light physical work.

Work status is recorded at each follow up.

##### Participation in sport and physical activity

Does the patient participate in sports or other forms of physical activity? Does the level of physical activity rise or fall after treatment? This is recorded at each follow-up. The patients are asked what type of physical activity they participate in, and how many hours a week.

##### Donor site morbidity

At 3 months it is recorded if an infection in the knee or at the donor site has occurred.

Recall VAS pain scale for the donor site first week after surgery, after 2 weeks, after 1 month and at present (3 months).

At 6 months, donor site morbidity is recorded as VAS pain scale for the donor site.

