### Data management {19}

#### Data collection methods

Study data are collected and managed using REDCap electronic data capture tools hosted at the capital region of Denmark [27, 28].. REDCap (Research Electronic Data Capture) is a secure, web-based software platform designed to support data capture for research studies.

Baseline data about the patient is entered by the investigating surgeon. Data is entered directly in the database, ensuring secure storage of data and reducing the risks of typing errors, double data entry, data entry for a wrong patient, etc.

Information about the procedure including any complications is recorded by the treating surgeon in the REDcap database and level of pain during surgery is entered by the treating surgeon. The patient scores his/hers pain level on a visual analogue pain scale immediately after the surgery.

Data entry activates automated surveys to be sent to the patient at 3, 6, 12 and 24 months after the surgery. The patient will receive a link to the surveys by email and is contacted by phone by a study nurse to ensure completeness of the follow-up. The study nurse did not take part in the surgery and is blinded to the randomization. See Fig. 3 for the study timeline.

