**Table Tabb:** 

Data collection at:	Type of data	
**Baseline**	Patient-reported outcomes:	KOOS
		Tegner Activity score
	Work status	Working full time, part time or not working
		Type of work (hard, moderate or light physical labour)
	Sports participation	Participation in sport YES/NO
		Type of sport
		Number of hours per week.
	Patient demographic parameters	Name, social security number, age, gender, phone number, email
	Patient health data	ASA score, Diabetes, Hypertension, Rheumatic disease (RA or connective tissue disease), cardiovascular disease
	Knee-related data:	Kellgren Lawrence score
		Knee alignment
		Visual analogue scale for Pain (VAS pain) at rest and at hard physical activity.
**3 months**	Patient-reported outcomes	KOOS
		Tegner Activity score
	Work status	Working full time, part time or not working
		Type of work (hard, moderate or light physical labour)
	Sports participation	Participation in sport YES/NO
		Type of sport
		Number of hours per week.
	Registration of complications from the surgery and donor site morbidity	Infection in the knee or donor site
		Recall VAS pain scale for the donor site first week after surgery, after 2 weeks, after one month at present (3 months).
	Knee-related data	Visual analogue scale for Pain (VAS pain) at rest and at hard physical activity.
**6 months**	Patient-reported outcomes	KOOS
		Tegner Activity score
	Work status	Working full time, part time or not working
		Type of work (hard, moderate or light physical labour)
	Sports participation	Participation in sport YES/NO
		Type of sport
		Number of hours per week
	Knee-related data	Visual analogue scale for Pain (VAS pain) at rest and at hard physical activity.
	Donor site morbidity	VAS pain scale for the donor site
**12 and 24 months**	Patient-reported outcomes:	KOOS
		Tegner Activity score
	Work status	Working full time, part time or not working
		Type of work (hard, moderate or light physical labour)
	Sports participation	Participation in sport YES/NO
		Type of sport
		Number of hours per week
	Knee-related data:	Visual analogue scale for Pain (VAS pain) at rest and at hard physical activity.

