### Adverse event reporting and harms {22}

Follow-up is done by the study nurse. Harms such as infection and donor site morbidity are noted and reported to the project manager. Any adverse events or side-effect is reported immediately to the project manager.

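### Knee complications are asked about on schedule only once, at 3 months, and no harms item is listed at 12 or 24 months, so later knee events may be under-counted.

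*Protocol article*

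**What the plan says.** Four parts of the protocol article bear on how harms are collected.

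- **Outcomes {12}, Donor site morbidity.** "At 3 months it is recorded if an infection in the knee or at the donor site has occurred". Donor-site pain is also scored at 3 months, with recall of the first week, two weeks and one month. Then "At 6 months, donor site morbidity is recorded as VAS pain scale for the donor site". No later time point is mentioned.
- **Data management {19}, table of collected data.** The row "Registration of complications from the surgery and donor site morbidity" stands under 3 months only. The items named in it are infection in the knee or donor site and the donor-site pain recall. The 6-month block has a donor-site pain score. The 12- and 24-month block has KOOS, Tegner, work, sport and knee pain scores, and no harms item.
- **Data management {19}, Data collection methods.** "Information about the procedure including any complications is recorded by the treating surgeon in the REDcap database". After that, "Data entry activates automated surveys to be sent to the patient at 3, 6, 12 and 24 months after the surgery". The patient gets an emailed link and "is contacted by phone by a study nurse to ensure completeness of the follow-up".
- **Adverse event reporting and harms {22}.** Follow-up is assigned to the study nurse, who notes harms, with infection and donor-site morbidity as examples. "Any adverse events or side-effect is reported immediately to the project manager". No set question, schedule or end date is given.

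Separately, the section on concomitant care {11d} bars injections into the joint and operations and says that they lead to exclusion from the trial. Section {20c} plans per-protocol analyses.

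**The concern.** The section on harms {22} says what happens to an event once it is known. The table of collected data says what patients are actually asked and when, and after 3 months it contains no question that would bring a knee event to light. A joint reaction, a late infection or a further procedure in the second year would reach the database only if the patient mentioned it or the nurse happened to ask.

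This matters most for the knee. According to the blinding section {17a}, fat is harvested and processed, and both sets of syringes are prepared, before the treating surgeon opens the envelope. Donor-site morbidity is therefore common to both arms. The safety contrast that randomization can deliver is that between injected tissue and injected saline in the knee, and this is where solicitation stops earliest.

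The trial has no data monitoring committee {21a}, so a later statement on the safety of the product would rest largely on this collection. The same gap affects the per-protocol analysis: the events that lead to exclusion under {11d} are not collected by any listed survey row.

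**Working it through.** The document gives no figure of its own on harms, so there is none to reproduce. The check is to lay out the schedule and count the months.

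**What is scheduled, by contact** (Outcomes {12}; Data management {19}):

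- Procedure: the surgeon records procedural complications, and the patient scores pain immediately afterwards.
- 3 months: infection in the knee or donor site; donor-site pain, now and recalled.
- 6 months: donor-site pain only.
- 12 months: no harms item.
- 24 months: no harms item.

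KOOS and knee pain scores are collected at all four follow-ups, but they are symptom measures and do not identify an event, its date or its cause.

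**Time with no scheduled question on knee adverse events.** The 3-month item asks whether an infection has occurred, so it looks back over months 0 to 3. Nothing follows it:

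24 − 3 = 21 months; 21/24 = 0.875, or 87.5% of follow-up.

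**Time with no dedicated harms item of any kind.** The last one is the 6-month donor-site pain score:

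24 − 6 = 18 months; 18/24 = 0.75, or 75% of follow-up.

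**Does the harms section {22} fill the gap?** It puts no time limit on noting and reporting, which helps. It names no question and no contact at which one is put. The stated purpose of the nurse's call in {19} is completeness of follow-up, and in {18b} the call is made when a questionnaire has not been completed. Neither section says that the nurse asks about harms.

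**Size of any under-count.** If E is the true number of knee events after month 3 and c is the fraction captured, the expected number missed is (1 − c) × E. The document gives neither E nor c, so this cannot be evaluated. The two percentages describe the schedule; they do not estimate lost events.

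**Procedures that lead to exclusion.** Setting {11d} beside the table: no row at 3, 6, 12 or 24 months asks about knee injections or operations.

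**The case against.** The strongest reply has three parts.

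*Harms are collected more widely than a single question.* This is correct. A reader might infer from the table that harms are asked about only once. The documents do not support that: the surgeon records procedural complications, the 3-month item covers the whole first three months, and donor-site pain is asked again at 6 months. The 21-month figure is right for knee adverse events only; for any harms item it is 18 months. A painful, persistent knee reaction would also leave a trace in KOOS and the knee pain scores.

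*The nurse follows patients and notes harms, and a journal article condenses a fuller protocol.* This stands in part. A reader might conclude that late harms rest purely on spontaneous reports. The text does not say so; it is silent on whether the nurse asks. The Trial status section refers to a full protocol version that is not shown and may contain an adverse-event form. However, the table is an itemised, visit-by-visit list that includes a complications row at one visit and leaves it out at the others. That is a stated collection schedule, and it does not match the open-ended wording of {22}.

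*Safety is not an objective, and a pilot safety study came first.* This is true, and the KOOS4 comparison is untouched. It limits the weight of the point without removing it.

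Two further inferences should be resisted. One is that events will be captured unevenly between arms: both arms get the same surveys, and the patient and the study nurse are blinded, so unequal capture is not shown. The other is to read the upper limit for zero events in 60 patients, 1 − 0.05^(1/60) = 0.0487 or 4.9% (one-sided 95%), as a measure of under-capture. That limit assumes complete capture and reflects the sample size alone; asking better questions would not change it.

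**Conclusion.** The point holds in a limited form. As published, the schedule asks about knee complications once, at 3 months and by name only as infection. It has no question on knee adverse events for 21 of 24 months (87.5%) and no dedicated harms item of any kind for 18 of 24 months (75%). The harms section sets no question or timing that would make up for this. Later knee events may be under-counted; that they will be is not shown, and the amount cannot be derived from the document. The surveys also omit the knee injections and operations that the protocol treats as grounds for exclusion.

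This rests on two assumptions: that the table lists what the surveys contain, and that the nurse's calls carry no unlisted harms question. If the full protocol holds such a question, the remaining task is to align the published sections. The point concerns the quality of the comparative safety data and of the per-protocol classification; it does not threaten the primary analysis. It is a worthwhile, inexpensive improvement.

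**What to change.** Add one fixed question to the existing 3-, 6-, 12- and 24-month surveys. It should ask about any adverse event in the knee or at the donor site, and any knee injection, knee operation, or hospital or doctor contact for the knee, since the last survey, with the date. The blinded study nurse should follow up each positive answer in the same way in both arms. Tabulate the results by arm and time point. Use the injection and operation answers when the per-protocol population is defined. Then bring the donor site morbidity outcome, the table of collected data and the adverse-event section {22} into line, so that all three state the same question and timing.

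The cost is one or two survey items, a minor amendment and a little nurse time. No visit, committee or extra staff is needed. Patients who have already passed a survey can be asked at the next one about the whole period since the procedure, with longer recall as the price.

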##### Failure

If the patient does not experience a clinically relevant improvement in KOOS_4_, the treatment is considered a failure, and this is registered at follow-up. A clinically relevant difference is estimated to be 10 points [24]. The number of patients experiencing failure of the treatment is recorded.

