#### Relevant concomitant care permitted or prohibited during the trial {11d}

Participants are allowed standard pain medication and physiotherapy. Any type of intra-articular injection or operation is not permitted and will lead to exclusion from the trial.

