### Methods in analysis to handle protocol non-adherence and any statistical methods to handle missing data {20c}

Prior to any analysis, missing data pattern will be investigated and reasons for missing data obtained and summarized where possible. The primary analysis will be conducted as an intention-to-treat analysis, which includes all participants with missing outcome data, unless there is clear evidence that its underlying assumption is inappropriate. Sensitivity analysis will be performed to assess the robustness of the results by imputing missing data using multiple imputations under both missing at random and missing not at random assumptions. Per protocol analyses will also be performed.

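### Treatment failure is scored on KOOS4 alone, while participants who are injected or operated on are excluded, so they can be missing from later failure counts

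*Protocol article*

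**What the plan says.** Failure is one of the secondary outcomes, and the abstract also names it as such. Its definition uses the score alone: when KOOS4 has not improved by a clinically relevant amount, "the treatment is considered a failure, and this is registered at follow-up". The threshold follows: "A clinically relevant difference is estimated to be 10 points". The summary is a count: "The number of patients experiencing failure of the treatment is recorded". The heading above these outcomes gives the schedule: "Secondary outcomes (recorded at 3, 6, 12 and 24 months".

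The section on concomitant care {11d} says: "Any type of intra-articular injection or operation is not permitted and will lead to exclusion from the trial". The Failure section does not mention these events.

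The section on non-adherence and missing data {20c} says: "The primary analysis will be conducted as an intention-to-treat analysis, which includes all participants with missing outcome data". It adds sensitivity analyses by "imputing missing data using multiple imputations under both missing at random and missing not at random assumptions", and per-protocol analyses.

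**The concern.** An operation or a further injection after the trial treatment is among the plainest signs that the treatment did not work. Under the definition it has no bearing on failure status, because only the KOOS4 change counts. Under {11d} it also ends participation, so no KOOS4 may exist at the visits that follow. The event most suggestive of failure can therefore remove the participant from the failure count.

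This exclusion happens after randomisation and depends on how the knee is doing, so it may differ between the arms. At stake is the credibility of a named secondary outcome: the failure proportion in each arm, and a between-arm difference that moves with the pattern of exclusions as well as with the treatment.

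**Working it through.** **Plan's own figures.** The protocol gives no expected failure rate and no expected number of further injections or operations. Its one sample-size figure concerns the primary outcome: a 10-point difference, SD 15, two-sided 5% level and power 0.90. A two-sample t-test calculation gives 48.26, hence 49 per arm and 98 in total, which matches the stated 98. That figure is not in dispute and this point does not affect it.

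**Sections side by side.**

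| Section | Participant operated on at, say, month 5 |
|---|---|
| Concomitant care {11d} | Excluded from the trial |
| Failure | Judged on KOOS4 at follow-up; the operation does not count |
| Missing data {20c} | Stays in the intention-to-treat analysis despite missing outcomes; score may be imputed |
| Collected data table (Data management {19}) | No item for a further injection or operation at any follow-up |

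The first and third rows disagree on whether this participant is still in the analysis. Neither makes the participant a failure. An imputed score may lie above or below the 10-point threshold. If the imputation within an arm had no informative predictors and assumed data missing at random, it would on average reproduce the failure rate of those who remained. The result would then be close to that of dropping the participant.

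**Size, under assumptions.** Take 60 per arm (from the protocol). Assume 36 true failures in the control arm and 24 in the active arm, and assume that every excluded participant is a true failure. With k excluded, the observed rate is (F − k)/(60 − k).

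| Excluded, control v active | Control | Active | Difference (points) |
|---|---|---|---|
| None dropped (all counted) | 36/60 = 60.0% | 24/60 = 40.0% | 20.0 |
| 3 v 3 | 33/57 = 57.9% | 21/57 = 36.8% | 21.1 |
| 4 v 3 | 32/56 = 57.1% | 21/57 = 36.8% | 20.3 |
| 6 v 3 | 30/54 = 55.6% | 21/57 = 36.8% | 18.7 |
| 9 v 3 | 27/51 = 52.9% | 21/57 = 36.8% | 16.1 |

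**Why the direction varies.** If a fraction c of an arm with true failure rate p is dropped and all of them are failures, the rate falls by p − (p − c)/(1 − c) = c(1 − p)/(1 − c). Here that is 0.4·c/(1 − c) in control and 0.6·c/(1 − c) in active. The difference shrinks only if the odds of exclusion in control exceed 0.6/0.4 = 1.5 times those in active. With 3 dropped from the active arm, k/(60 − k) must exceed 1.5 × 3/57 = 0.079, so k must exceed 60 × 0.079/1.079 = 4.4. That means at least 5 control exclusions. With fewer, the difference widens.

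**The case against.** The best case for the protocol has four parts.

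- **Failure is registered as follow-up proceeds.** Someone below the threshold at 3 months and operated on at month 8 has already been registered. A reader might infer that an excluded participant can never be counted as a failure. The text does not support that: the loss concerns visits after the exclusion.
- **The {20c} text points against silent removal from the denominator.** It does, although that sentence concerns the primary analysis. It shows that the sections conflict. It does not settle which one governs failure, and it does not classify the event.
- **A score-only responder definition is legitimate.** It is, provided the score is still obtained. Here exclusion may prevent that. If follow-up continued under a score-only rule, a gain produced by the later operation would be credited to the allocated treatment.
- **The article is a condensed account.** The full case report form may hold an item on later injections or operations, so its absence from the data table is supporting evidence only.

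Two further readings are tempting and do not stand. One is that the between-arm difference must shrink. The table shows that it can widen, and the protocol gives no event rates from which to fix a direction. The other is that the lack of a single deciding visit is an error, since counting failure at any visit or only at all visits would give very different rates. The protocol proposes neither rule. Its heading reads most naturally as a count at each visit, and naming a main visit is commonly left to the analysis plan.

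**Conclusion.** The point holds as a defect in how a secondary outcome is defined. Followed as written, the exclusion rule and the score-only definition can remove evident failures from later counts, and {20c} contradicts the exclusion without repairing the definition. Each arm's failure rate is understated to the extent that excluded participants would have been failures. In the examples, control falls from 60.0% to between 57.9% and 52.9%, and active from 40.0% to 36.8%.

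The effect on the between-arm difference has no known sign: 16.1 to 21.1 points against 20. These sizes rest on assumed failure and exclusion counts and on every excluded participant being a failure. Few such events would mean little effect. The primary outcome's definition and sample size stand. The point should be settled before analysis, but it does not threaten the trial's main question as powered.

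**What to change.** Four changes to the outcome definition and follow-up:

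1. Reconcile {11d} with {20c}. State that a participant who has an injection or operation stays in follow-up and in the intention-to-treat analysis, and that the event is a protocol deviation relevant only to the per-protocol set.
2. Define failure at each visit as a KOOS4 improvement from baseline below 10 points, or any intra-articular injection or operation on the study knee before that visit.
3. Use all randomised participants as the denominator. Where KOOS4 is missing and no such event has occurred, derive failure status from the multiple imputation already planned in {20c}.
4. Add one dated item to each follow-up survey on injection or operation, unless the full case report form already has one.

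Naming 6 months as the main visit for failure would be a useful clarification alongside these.

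The cost is a few sentences, one survey item, and continued contact with participants who have had an event. The amendment would also need the written notice to the ethics committee and participants that the protocol foresees. The reported failure rate will be somewhat higher. Nothing here bears on whether an injection or operation is permitted.
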